### Aim

This study has 4 main objectives. First, it aims to enhance nursing students’ EI by helping them better recognize and understand their own emotional responses and those of others, using reflective and interactive simulations. Second, it seeks to strengthen students’ crisis management abilities through virtual patient scenarios that simulate high-stress situations, allowing them to practice appropriate coping and decision-making strategies. Third, the project aims to improve student engagement and motivation by integrating game-based and AI-enhanced learning, assessing their impact on participation, interest, and satisfaction. Finally, the study intends to provide empirical support for innovative nursing education by establishing a framework that combines game-based pedagogy with AI simulation to meet the evolving demands of clinical practice. This approach integrates practice and research through iterative cycles of planning, action, observation, and reflection to address real-world instructional challenges and support continuous improvement.

## Methods

### Overview

The innovative teaching strategy in this project integrates traditional classroom lectures, clinical case discussions, and instructional video analyses with additional components such as GBL, hands-on technical practice, and interactive software using AI virtual humans. These combined approaches aim to support nursing students in developing EI—particularly self-awareness and emotion recognition regulation—along with empathic communication skills. Furthermore, students will engage in suicide risk assessment training with virtual patients representing various psychiatric conditions.

This teaching research project aims to explore how the integration of game-based pedagogy and AI virtual human interaction can enhance nursing students’ EI and psychological crisis management abilities. To achieve this, the study will use an action research methodology involving 2 iterative cycles. After implementing the first cycle and collecting both quantitative and qualitative data, revisions will be made to the intervention based on the findings before initiating the second cycle. Each cycle will incorporate a single-group pretest-posttest design to evaluate the effectiveness of the intervention using quantitative measures. Through this iterative process, the study seeks to optimize the impact of innovative teaching methods on students’ learning outcomes. The research design flowchart is shown in Figure 1.

**Figure 1 figure1:**
[figure not shown]
Research flowchart. AEIS: Adult Emotional Intelligence Scale; PI: principal investigator.

### Phase 1: Development of an Innovative Teaching Plan Incorporating Generative AI Virtual Humans

During this phase, generative AI technologies will be applied to develop 5 AI virtual human simulation scenarios, which will be hosted on the platform provided by HTC. These include 1 scenario focused on empathic communication skills and comprehensive assessment of 5 core psychiatric domains, those scenarios representing different psychiatric diagnoses or clinical conditions: major depressive disorder, bipolar disorder (depressive episode), schizophrenia, substance use disorder, and borderline personality disorder. Each scenario will feature AI-simulated patients exhibiting suicide ideation and behaviors associated with suicide risk.

The principal investigator has obtained certification as a seed instructor for immersive VR teaching scenario development through the HTC medical VR program (Virti VR platform). Accordingly, the project will use the Virti AI virtual human platform to design intelligent, interactive case scenarios using generative AI. The content of the 5 scenarios will undergo expert panel review by 3 psychiatric mental health nursing professionals and the principal investigator. These expert consultations will guide revisions to ensure that the simulation scenarios accurately reflect realistic communication patterns and clinical presentations found in psychiatric settings.

Once the AI virtual human scenarios are finalized, students will be able to access them anytime and anywhere during phase 2 via the web-based platform. They will engage in interactive simulations with virtual psychiatric patients, practicing empathic communication, emotion recognition, and skills in psychological crisis and suicide risk assessment. All student-AI interactions will be automatically recorded on the backend of the system to facilitate evaluation and scoring by instructors.

### Phase 2: Implementation Phase—Integrating GBL and Generative AI Virtual Human Instruction (2 Action Research Cycles With Pretest-Posttest Evaluation in Each Cycle)

#### Design

This teaching research project adopts an action research methodology, which is a practice-oriented and participatory approach that emphasizes solving real-world problems through iterative cycles of planning, action, observation, and reflection. Action research is widely applied in diverse fields, including education, health care, management, and the social sciences. At its core, it involves close collaboration between researchers and participants to implement systematic actions and evaluations that lead to both practical improvements and theoretical development [18]. In recent years, action research has been increasingly recognized as a “multimethodology” approach due to its flexibility in integrating both qualitative and quantitative methods to address complex problems [19]. The typical process of action research consists of five key steps: (1) identifying the problem and defining the research objectives; (2) planning the action, including designing the intervention and anticipating possible outcomes; (3) implementing the action and collecting relevant data; (4) evaluating the outcomes to determine whether the objectives have been achieved; and (5) reflecting on and refining the action plan for subsequent cycles. The strengths of action research lie in its practical orientation and its participatory nature, which fosters the growth of knowledge and skills among participants [20].

EI refers to the ability to perceive, understand, and manage one’s own emotions as well as those of others. Its core components include self-awareness, self-regulation, social awareness, and relationship management [21]. In recent years, EI has gained widespread attention in both educational and clinical psychology domains. In Taiwan, researchers have developed a culturally adapted Adult Emotional Intelligence Scale (AEIS) [22], which has demonstrated strong reliability and validity in both nursing professionals and university student populations. Higher total scores on the AEIS indicate greater EI [22]. Accordingly, this teaching research project will be conducted through 2 iterative action research cycles. A single-group pretest-posttest design will be used for the quantitative component, while qualitative data will be collected through student reflective writings and classroom observations to analyze their emotion awareness, communication behaviors, and responses to the teaching intervention.

#### Sampling and Recruitment

Participants will be recruited from third-year nursing students enrolled in the Mental Health and Psychiatric Nursing course at a university in Taiwan. Convenience sampling will be used. The inclusion criteria are as follows: (1) students must be aged at least 20 years; and (2) they must be currently enrolled in the course, voluntarily agree to participate in the study, and be willing to complete both the pretest and posttest AEIS questionnaires as well as submit a written reflection. Students who have suspended their studies or are on academic leave at the time of recruitment will be excluded. Recruitment will be conducted through in-class announcements and information sheets provided by the course instructor. All participants will receive detailed explanations about the study procedures and their rights, and written informed consent will be obtained before participation.

#### Data Collection and Analysis Plan

This study adopts a single-group pretest-posttest design implemented across 2 instructional cycles (first and second semesters). Quantitative data will be gathered with the AEIS—a validated 26-item instrument covering 4 subscales: emotion awareness (items 1-7), emotional expression (items 8-12), emotion regulation (items 13-17), and emotional use (items 18-26). Each item is scored on a 4-point Likert scale (ranging from 0=strongly disagree to 3=strongly agree); higher scores denote greater EI [22]. Permission to use the AEIS has been obtained from the original author. The scale will be administered in week 3 (pretest evaluation) and week 16 (posttest evaluation) of each semester. Qualitative data will consist of students’ reflective reports—collected throughout both cycles—and classroom observations conducted in week 17 to document behavioral engagement during gameplay and AI-patient interactions.

At the item level, AEIS subscale scores will be prorated when no more than 1 item per subscale is missing; otherwise, the subscale will be set to missing. At the record level, patterns of missingness will be inspected with the Little MCAR test [23]. As linear mixed effects models (LMMs) provide unbiased estimates under a missing-at-random assumption, incomplete cases will be retained in the primary analyses. For ancillary paired sample 2-tailed *t* tests or Wilcoxon signed-rank tests, missing posttest values will be multiply imputed (20 imputations using predictive mean matching); the imputed results will be pooled following the rules formulated by Rubin [23] and compared with complete-case outputs as a sensitivity check.

Descriptive statistics (means and SDs or medians and IQRs) will be reported for all variables. The normality of pretest-posttest difference scores will be checked with the Shapiro-Wilk test. If the distribution is normal, within-participant changes in AEIS total and subscale scores will be analyzed with paired sample 2-tailed *t* tests; otherwise, the Wilcoxon signed rank test will be used. Effect sizes will be expressed as Cohen *d* with 95% CIs. To compare change trajectories between cycles, an LMM with random intercepts for participants will be fitted, including fixed effects for time (before the intervention vs after the intervention), cycle (1 vs 2), and their interaction (time × cycle). Holm-Bonferroni adjustment will control the family-wise error rate across AEIS subscales. All analyses will follow an intention-to-treat principle (participants with ≥1 posttest record retained); sensitivity checks with complete-case data will evaluate robustness. Statistical significance is set at α=.05 (2-tailed). Analyses will be conducted in SPSS software (version 29.0; IBM Corp) and R (version 4.4.0; R Foundation for Statistical Computing; *lme4* package for LMMs).

To capture students’ experiences and perspectives, we collected qualitative data through structured reflective reports and oral and written feedback after the implementation of the innovative teaching practices. Each student was required to complete a reflective report structured around 5 open-ended questions aligned with the core learning domains of self-awareness, emotional self-awareness, social awareness, empathic communication, and crisis management competence; for example, students described personal insights gained from participating in the card-based educational game, emotional reactions experienced during gameplay, and strategies for recognizing and responding to peers’ emotional cues. They also reflected on their ability to demonstrate empathy in simulated dialogues with AI virtual patients and articulated how these experiences contributed to their confidence in managing psychological crises. Each reflective entry was expected to exceed 100 Chinese characters, thereby encouraging deeper engagement and detailed narrative accounts of their learning processes.

In addition to written reflections, student oral and written feedback were gathered during debriefing sessions immediately after the teaching interventions. These interactive discussions invited participants to share their impressions of the AI virtual patient encounters and the gamified learning with card play, highlighting both challenges and perceived benefits. Students frequently commented on the authenticity of the AI-driven dialogues, which prompted them to practice empathic responses, and on the playfulness of the card game, which fostered self-discovery and peer interaction. Oral and written feedback not only provided spontaneous, unstructured accounts but also allowed for triangulation with the reflective reports, offering complementary insights into how the innovative teaching strategies shaped EI and learning engagement. Together, these qualitative materials provided a rich and multifaceted dataset for thematic analysis, illuminating both individual developmental trajectories and collective learning dynamics within the cohort.

During the practical sessions with AI virtual patients, investigators used structured observation rubrics to evaluate student performance across five domains: (1) the ability to recognize the patient, introduce themselves, and demonstrate proactive caring; (2) the use of appropriate communication skills during interviews or technical procedures; (3) the demonstration of empathy in patient interactions; (4) the accuracy of relevant assessments such as symptom evaluation or suicide risk assessment; and (5) the quality of group reflective sharing after practice. Each domain was equally weighted at 20 points, for a total of 100 points in the rubric.

Student reflection reports and student oral and written feedback from the implementation of the innovative teaching practices and observation notes will be thematically analyzed in NVivo 14 (Lumivero) using the 6-step framework proposed by Braun and Clarke [24]. The analysis will proceed systematically through 6 phases: (1) familiarization with the data through repeated reading and note taking, (2) generating initial codes across the dataset, (3) searching for candidate themes by collating codes, (4) reviewing themes in relation to both coded extracts and the entire dataset, (5) defining and naming themes to refine their scope and focus, and (6) producing a coherent report with representative extracts. To ensure rigor and transparency, coding decisions will be documented in an analytic memo trail, and at least two researchers will independently code a subset of data before discussing discrepancies to enhance reflexivity and credibility. The analytic approach will follow recent guidance that emphasizes active, reflexive engagement by the researcher rather than striving for consensus coding or reliability metrics, thereby acknowledging the researcher’s interpretative role in meaning making [24]. In addition, Braun and Clarke [25] highlighted common pitfalls and provided 10 recommendations for producing methodologically coherent thematic analysis, underscoring the importance of distinguishing between topic summaries and interpretative meaning-based themes. Their commentary further emphasizes that researchers must “own” their perspectives, ensuring that analytic practices remain theoretically consistent with the chosen thematic analysis approach [25]. Qualitative findings will be triangulated with quantitative results to elucidate mechanisms underlying observed changes in EI and learning engagement.

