### Sample Size and Power Analysis

Using G*Power 3.1 (Heinrich Heine University) for a paired sample 2-tailed *t* test (“Means: difference between two dependent means, matched pairs”), we set α=.05, desired power=.80, and a medium anticipated effect size of Cohen *d*=0.50—consistent with meta-analytic estimates for short educational interventions targeting EI. The calculation yielded a required completer sample of 32 students to detect the pretest-posttest difference with 80% power. Allowing for typical nursing-course attrition of 15% to 20%, we plan to recruit 40 participants per cycle, ensuring that at least 32 remain for posttest analysis.

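### The analyses have incompatible roles: the mixed model is linked to the primary analyses but its only stated purpose is to compare cycles, while the 80% power belongs to a paired test called ancillary

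*Protocol article*

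**What the plan says.** Three statements in the protocol bear on which analysis decides the question.

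- **Label.** Data Collection and Analysis Plan, in its paragraph on missing data: "As linear mixed effects models (LMMs) provide unbiased estimates under a missing-at-random assumption, incomplete cases will be retained in the primary analyses". The next sentence calls the paired t tests and Wilcoxon signed-rank tests ancillary.
- **Purpose.** The next paragraph of that section assigns within-student change in AEIS total and subscales to the paired tests. The LMM comes in for a different job: "To compare change trajectories between cycles, an LMM with random intercepts for participants will be fitted", with fixed effects for time, cycle and time × cycle.
- **Power.** Sample Size and Power Analysis uses the G*Power option "Means: difference between two dependent means, matched pairs": "we set α=.05, desired power=.80, and a medium anticipated effect size of Cohen *d*=0.50". It concludes: "The calculation yielded a required completer sample of 32 students to detect the pretest-posttest difference with 80% power". Recruitment follows from that: "Allowing for typical nursing-course attrition of 15% to 20%, we plan to recruit 40 participants per cycle".

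On multiplicity the plan says "Holm-Bonferroni adjustment will control the family-wise error rate across AEIS subscales". It states no adjustment or hierarchy for the total score, the two cycles or the LMM terms.

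The section on cycle 2 states that it enrols a new cohort and uses content revised after cycle 1.

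**The concern.** Read literally, the primary model serves a between-cycle comparison that has no power statement, and the only powered test is ancillary. The study's main question, whether the teaching model improves emotional intelligence, has no named deciding test.

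Two things are at stake. First, a reader would credit the 80% to whatever is reported as primary, and for the comparison the LMM is said to serve that figure would be well off. Second, several total-score results would be available without an order among them: a paired test in each cycle, and the LMM terms. The Results section plans a preliminary analysis by the end of cycle 1, so the choice could be made after data have been seen.

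The cycle comparison is also poorly suited to carry a conclusion. Cycle differs by cohort, by semester and by revised content all at once.

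**Working it through.** **Inputs from the protocol.** Two-sided α=0.05, power 0.80, d=0.50 for within-student change, 32 completers, attrition 15% to 20%, 40 recruited per cycle, different students in each cycle.

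**Assumptions not in the protocol.** Between-cycle differences of 0.25 and 0.50 SD of change, equal SD of change in both cycles, 32 completers in each cycle, and complete pre-post pairs.

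**1. The plan's own figure.** Normal approximation: n = ((1.960 + 0.842)/0.50)² = 31.4, rounded up to 32. The exact noncentral t gives 34, with power 0.782 at n=32. Attrition: 32/0.85 = 37.6, so 38; 32/0.80 = 40. The 32 and the 40 are reproduced closely enough, as figures for a paired test.

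**2. If time × cycle is primary.** With one pre and one post value per student and independent cohorts, the interaction is a two-sample t test on change scores. The noncentrality is D/√(1/32 + 1/32) = 4D, with 62 df.

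| Difference in change, D (SD of change) | Noncentrality | Power |
|---|---|---|
| 0.25 | 1.0 | 0.166 |
| 0.50 | 2.0 | 0.504 |
| about 0.71 | about 2.85 | 0.80 |

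For 80% power at D=0.50, 64 completers per cycle would be needed, against 40 recruited. The detectable 0.71 SD exceeds the whole pre-post effect that the plan assumes.

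**3. If a pre-post contrast from the same LMM is primary.**

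- Within one cycle, with the variance of change pooled over cycles: noncentrality 0.50 × √32 = 2.83, 62 df, power 0.795. The paired t test in that cycle gives 0.782 (31 df).
- Averaged over both cycles, 64 completers, d=0.50 in each: noncentrality 0.50 × √64 = 4.0, power 0.976.

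**4. Error rate for the total score, if any significant test could count as success.** The two per-cycle tests use independent students: 1 − 0.95² = 0.0975. Adding the interaction brings this to about 0.11 by simulation under no effect (32 per cycle).

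**The case against.** The strongest reply is that the sentence about primary analyses is a rule for missing data and does not name a primary effect. No section says that time × cycle decides the study. The model also contains a time effect, so it can estimate pre-post change, and the Methods frame the evaluation as a pretest-posttest comparison in each cycle. On that reading the power carries over almost intact (0.795 against 0.782). This stands, and it limits the point. A reader might infer that the stated power is simply wrong for the primary comparison. The text does not support that, because it never says which LMM effect is primary.

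Three other stronger readings also go too far.

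- **Coding.** One could say that R's default coding would return the cycle 1 change in place of the overall effect. The protocol specifies no coding, and that detail commonly belongs in an analysis plan. It is not an error in this document.
- **Error rate near 20%.** That needs a separate pooled test, which the plan does not define, Holm-adjusted subscale families repeated across analyses, and a rule that any significant result wins, which the plan does not state.
- **No adjustment at all.** The four subscales do have Holm.

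It is also fair to say that pooling over cycles is partly a choice, since the intervention is revised between them.

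The mismatch itself is not answered. The label, the stated purpose and the power calculation do not point to the same test, and a more detailed analysis plan would have to overrule at least one of these statements.

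**Conclusion.** The concern holds as an inconsistency in roles. The LMM is tied to the primary analyses and given only the between-cycle purpose, while the 80% power belongs to a paired test labelled ancillary.

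The consequence is conditional on the reading. Power is about 50% at 0.50 SD and 17% at 0.25 SD if time × cycle is primary. It is about 80% per cycle, or 97.6% averaged over cycles, if a pre-post contrast is primary. The planned sample is therefore adequate for the question the study asks, provided the plan names that question's test. The error rates of just under 10% and about 11% apply only if any total-score result may be claimed as success, which the text neither states nor excludes.

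This should be corrected. It does not call for more students.

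**What to change.** Reconcile the three statements by naming one primary test: the pre-post change in AEIS total, as an explicit contrast from the LMM, two-sided α=0.05. One option is the change averaged over both cycles, acknowledging that it averages the first-semester and the revised intervention. A named per-cycle contrast would also remove the contradiction. Then:

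- restate the power for that contrast (97.6% at d=0.50 with 64 completers if averaged);
- keep the four subscales as secondary, with Holm applied to the same contrast;
- report time × cycle and the remaining per-cycle changes as estimates with 95% CIs, and attribute any cycle difference to cohort, semester and revision together;
- describe the paired tests consistently as supportive.

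The cost is a few sentences and a rewritten power paragraph. The drawback is that per-cycle p values lose confirmatory status. Cycle 1 is under way, so the wording should be fixed before the preliminary analysis at the end of that cycle.

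### Rubin pooling is not defined as written for the Wilcoxon branch, and a Shapiro-Wilk pretest lets the test differ between AEIS scores and cycles

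*Protocol article*

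**What the plan says.** All the analysis statements are in the Protocol article, Data Collection and Analysis Plan.

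- **Imputation.** For the ancillary paired t tests or Wilcoxon tests, missing posttest values are multiply imputed ("20 imputations using predictive mean matching"). Then "the imputed results will be pooled following the rules formulated by Rubin", and the results are compared with complete-case output. One pooling rule covers both tests.
- **Choice of test.** "The normality of pretest-posttest difference scores will be checked with the Shapiro-Wilk test". If normality holds, change in the AEIS total and subscales is analysed by paired t test; "otherwise, the Wilcoxon signed rank test will be used".
- **Effect measure.** Cohen d with a 95% CI, whichever test is used.
- **Role of the mixed model.** Incomplete cases are kept in the primary analyses on the strength of the linear mixed-effects model (LMM). The LMM is then given the comparison of change between cycles, and within-participant change goes to the paired tests.
- **Analysis set.** Participants with at least one posttest record are retained.

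Under Sample Size and Power Analysis, the only calculation is for a paired t test: "we set α=.05, desired power=.80, and a medium anticipated effect size of Cohen" *d*=0.50. "The calculation yielded a required completer sample of 32 students".

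**The concern.** Rubin's rules combine, across imputed data sets, an estimate and its variance. The signed-rank test as named returns neither. If normality is rejected, the analyst must devise a way to pool after seeing the data, and different devices give different results.

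The pretest adds a second data-driven step. Nothing fixes one test for all scores or for both cycles, and the section does not say whether the check uses complete cases or imputed data. One AEIS score may be tested on its mean change and another on ranks, or the same score differently in the two cycles. A rank-based P value can then stand beside a mean-based Cohen d, in a study sized for the mean difference. At stake are the prespecification of the within-cycle tests and, if changes are skewed, their error rate for zero mean change.

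**Working it through.** **1. The plan's own figure.** Inputs from Sample Size and Power Analysis: two-sided α = 0.05, power 0.80, d = 0.50.
- Normal approximation: n = ((1.960 + 0.842)/0.50)² = 31.4, rounded up to 32. This matches the stated 32.
- Exact noncentral t: n = 34, with power 78.2% at n = 32. The gap of two students is small and is not the point here.
- Attrition: 32/(1 − 0.20) = 40, as planned. With 40 recruited, 15% to 20% attrition means 6 to 8 missing posttests.

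The sample size therefore rests on the paired mean difference.

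**2. What each branch gives Rubin's rules.** With m = 20, the rules need an estimate Qᵢ and a variance Uᵢ from each imputed set. The pooled estimate is the mean of the Qᵢ, and the total variance is T = mean(Uᵢ) + (1 + 1/20)·B, where B is the variance of the Qᵢ between imputations.
- Paired t test: Qᵢ = mean change, Uᵢ = SE². Defined.
- Signed-rank test: a rank statistic and a P value. No Qᵢ or Uᵢ is named.

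The gap can be filled, but not in only one way. In one simulated data set (40 students, 8 posttests imputed, skewed changes):

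| Pooled quantity | Estimate | SE | Ratio |
|---|---|---|---|
| Hodges-Lehmann shift, SE from its CI | 0.83 | 0.64 | 1.29 |
| Signed-rank z, unit variance | 1.46 | 1.08 | 1.35 |
| Mean change | 1.18 | 0.68 | 1.73 |

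The plan selects neither rank-based device.

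**3. How often the pretest splits the scores.** Five scores (total and four subscales) in two cycles make 5 × 2 = 10 checks. If all changes are normal and the checks independent, P(at least one rejection at 0.05) = 1 − 0.95¹⁰ = 0.401. Independence is an approximation, since the total is the sum of the subscales. A simulation with correlated subscales built from 0-3 items and 32 completers per cycle gave 62% of studies not using one test throughout. In 60%, at least one score was tested differently in the two cycles. The documents give no AEIS SD or correlation, so the item model is assumed.

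**4. What the pretest does to the error rate.** Simulated two-sided rejection rates for zero mean change, complete data, n = 32:

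| Changes (assumed) | t test always | Shapiro-Wilk, then t or Wilcoxon |
|---|---|---|
| Normal | 4.5% | 4.7% |
| Five-item 0-3 Likert sums | 5.2% | 5.4% |
| Gamma, shape 6 | 5.4% | about 6.6% |
| Gamma, shape 2 | 5.7% | 10.2% |

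Under skew the signed-rank test addresses a different null (symmetry about zero), so it can reject when the mean change is zero. At d = 0.50, power with the pretest against the t test alone was 78.4% against 78.5% (normal), 77.6% against 78.4% (Likert sums) and 76.0% against 81.3% (gamma shape 6).

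**The case against.** The strongest reply is that these tests are ancillary, the LMM needs no imputation, and an article may leave the pooled quantity to a fuller plan. The first two parts stand and limit the consequence. The third stands only in part: the article does state a pooling rule, and the rule does not fit one of the two tests that it names. The paired test is also the one that the study is sized on and the one assigned to within-participant change.

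Four stronger readings are tempting, and the documents do not support them.

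- **That the pooling is impossible.** It is not: a Hodges-Lehmann shift or a normalised z can be pooled. The defect is that neither is named.
- **That the 20 imputed sets will give conflicting normality verdicts.** This assumes that the check is rerun in each set, which the plan does not say; one check on observed differences is a natural reading. It also assumes that whole posttests are imputed. The retained set requires at least one posttest record, and with one posttest per cycle and a new cohort in cycle 2, that leaves mainly subscales set to missing. No disagreement rate is relied on here.
- **That mixing tests invalidates the Holm adjustment.** Holm is valid for any set of valid P values.
- **That the cycle comparison is compromised.** That comparison is the time × cycle term of the LMM, not one cycle's P value against the other's.

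A common Cohen d does give one effect metric throughout, which is useful. It simply does not correspond to the rank test. It is also fair that, for normal or Likert-sum changes, the pretest hardly alters decisions.

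**Conclusion.** The point holds in a limited form. The pooling rule is undefined as written for the Wilcoxon branch, and the Shapiro-Wilk step allows different tests across scores and cycles, with about a 40% chance of at least one false rejection in 10 checks under normality and independence. The cost in error rate is negligible when changes are normal or Likert-like. It is modest under mild skew (about 6.6% against 5.4%) and clear under stronger skew (about 10% against 6%). The skewed models are assumptions; the documents do not show how AEIS changes are distributed. The primary LMM is not affected. The change should be made, because it is cheap and concerns the test behind the sample size, but the study's main conclusions do not hang on it.

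**What to change.** In Data Collection and Analysis Plan:

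1. Remove the Shapiro-Wilk step. Analyse mean change by paired t test for the AEIS total and every subscale in both cycles, as the ancillary analysis to the LMM.
2. In the imputed analysis, pool the mean change and its standard error by Rubin's rules with small-sample degrees of freedom.
3. Report the Wilcoxon test for every score on complete cases as a sensitivity check. If it is kept in the imputed analysis, name the pooled quantity and its variance, for example the Hodges-Lehmann shift with its SE.
4. Reconcile the imputation of missing posttests with the rule that retains only participants who have a posttest record. State which students and which values are imputed.

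The cost is wording only, with no change to sample size or data collection. The downside is reliance on the robustness of the t test with about 32 bounded change scores per cycle, which the Wilcoxon sensitivity check covers.
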